#### Allocation concealment and blinding

Study staff enrolling participants at bedside are responsible for completing the baseline assessment, confirming eligibility with a site principal investigator, and informing participants and the intervention team to which arm they have been randomized. Allocation concealment will be achieved by the use of a computer-based randomization mechanism. Stratification factors across 6 different sites will further obscure any ability to predict allocation. Because the intervention is a clinical team intervention, participants cannot be blinded to receipt of the intervention. Study staff conducting follow-up assessments will not be blinded to treatment assignment.

### Intervention: SIRI team arm

Participants randomized to the intervention receive integrated infectious disease and SUD care (SIRI team) both during the hospitalization and after hospital discharge for 4 months post-randomization. The intervention is based upon six general principles for treating PWID with infectious complications and is informed by harm reduction.*Medications for SUD as integral to management of infectious complications* [20–22, 25, 37–39]– The intervention team will offer to initiate and continue/maintain medications for OUD and other SUDs in a low-barrier fashion, as indicated in standard clinical care, with a focus on harm reduction. If the participant accepts the medication, the team will facilitate inpatient initiation of medications as well as manage these treatments in the post-hospital intervention period.*Integration of ID and SUD care* [9, 40–42]– A single team provides consultation for both ID and SUD care for hospitalized participants. During the hospital stay, this promotes holistic and realistic decision-making regarding infectious disease treatment plans. After discharge, the team serves as a one-stop-shop for addressing participant medical and social needs, with a focus on ensuring the infection is being treated and the harms of substance use are mitigated.*Longitudinal care with familiar providers* [36, 43, 44]– Medical mistrust is common among PWID due to near-universal experience of stigma and discrimination in the healthcare system. The same specialized treatment team, experts in providing sensitive and culturally competent care to PWID, follow participants from the hospital setting and beyond into the community. The team serves as the ID and SUD treatment service both during and after hospitalization.*Multidisciplinary care and care coordination* [45–48]– Hospital medical, nursing, and case management teams are often inexperienced in caring for PWID and helping to meet their unique needs. The intervention team serves an important role in coordinating care, ensuring appropriate treatment of participants, and helping facilitate therapeutic discharge plans.*Tailored antibiotic options and care settings* [25, 28, 29, 49, 50]– The team chooses from antibiotics that are considered standard clinical care but may decrease the need for extended hospitalization or utilization of peripherally inserted central catheters. The treatment team ensures the best antibiotic plan for each individual in the context of the available ID literature, while taking into account the individual’s substance use and social circumstances.*Harm reduction* [33, 34, 51–56]- Many patients hospitalized with SIRIs do not want to cut down or stop using drugs, and for those that do, complete abstinence can be difficult to achieve. Applying harm reduction to the care of patients with SIRI is critical to facilitating complete infection treatment and avoiding preventable drug-associated morbidity and mortality. Harm reduction informs how the intervention is delivered as well as the outcomes measured.

#### SIRI team inpatient care

After randomization to the intervention group, participants receive the clinical services of the SIRI team for up to 4 months. The SIRI team evaluates the participant and provides consultatory care for participants in concert with their primary medical or surgical team. Infectious disease care includes assistance in diagnosis and management of the qualifying acute bacterial or fungal infection. In contrast to a typical ID consult service, the SIRI team will assist in management of SUD. This integration includes performing a substance use history, evaluation, diagnosis of SUDs, and recommendations for management of SUD, based on the participant’s willingness (or readiness) to manage their substance use. The SIRI team will also be involved with managing other symptoms associated with SUD and acute infections including pain and anxiety. Due to individuals’ acute medical needs, participants may have already received consultative services from infectious disease or addiction medicine physicians before they enroll in the study. In these cases, the intervention team will discuss with both services to facilitate a warm handoff of care to the SIRI team.

The SIRI team employs an inpatient harm reduction protocol to screen, treat, and prevent other infectious diseases common among PWID. The team also aims to reduce overdose by ensuring access to naloxone. Participants living with HIV are offered inpatient initiation of anti-retroviral therapy (ART). For participants with chronic hepatitis C, all baseline labs and studies are obtained, as part of usual clinical care, to facilitate treatment in the outpatient setting. Participants with indications for hepatitis A or B vaccination are offered these vaccines during the hospitalization. Participants without HIV infection will be educated on pre-exposure prophylaxis (PrEP). For those interested, PrEP is prescribed upon hospital discharge or they may be navigated to another local PrEP provider.

Other inpatient services provided by the SIRI Team that fall outside the standard of care for most typical hospital-based ID consult services include the following: 1) Close coordination and frequent communication with hospital case manager/social worker to help guide discharge planning; 2) working to identify funding sources for post-hospital medications and follow-up services; 3) facilitating access to a box of intranasal naloxone immediately before or after discharge; 4) prescribing necessary post-discharge medications, pick-up from pharmacy, and delivery to participants.

If a participant is readmitted to the same hospital during the 4-month intervention period, the intervention team will re-engage with them in the hospital and again provide SIRI team care. If a participant is admitted to a different hospital during the intervention period, the SIRI team will attempt to coordinate with physicians in the non-index hospital to help coordinate post-hospital care. Similarly, while SIRI team provider will not be able to directly provide care to participants while incarcerated, they may attempt to advocate for individuals and communicate with providers in the department of corrections.

#### SIRI team post-discharge care

After hospital discharge, the SIRI team continues to care for participants until 4 months after randomization. Based on the median length of stay, the expected post-hospital period will be at least 3 months. In addition to their role as a care navigator and counselor, the patient navigator serves to facilitate low barrier communication with the medical providers. Meetings may occur in person as formal clinic visits, drop-in clinic hours, videoconference, telephone/text messaging, or “home” visits by the patient navigator.

Key evidence-based harm reduction interventions include overdose education and naloxone distribution, referral to SSPs (if available), discussion of safer injection practices, navigation to PrEP services, and low barrier access to MOUD [33, 51]. For participants with OUD, the team manages MOUD directly and helps ensure linkage to methadone programs for those utilizing methadone. The SIRI team works to identify local substance use treatment programs, including those offering contingency management for stimulant use disorder. If local or app-based contingency management programs are available to participants, the SIRI team will help navigate participants to these programs as part of standard clinical care.

The SIRI team will provide care in whichever modality is feasible throughout the intervention period. This may include traditional clinic visits, street medicine, home visits, visits to residential addiction treatment, and telehealth encounters, among others.

#### Patient navigator component

The patient navigator approach includes five functions: 1) establishing an effective working relationship with the participant; 2) encouraging identification and use of strengths, abilities, and assets; 3) supporting participant control over goal setting and the search for needed resources; 4) viewing the community as a resource and identifying informal sources of support; and 5) conducting case management as an active community-based activity.

The patient navigator goals are to assess and assist participants in four primary domains: 1) Medical: Patient navigators facilitate participants completing antibiotic therapy for their acute infection and help participants meet other medical needs, such as getting to medical appointments, managing medications, and encouraging adherence to treatments. 2)

Substance use: Patient navigators use motivational interviewing techniques to ascertain barriers and facilitators to reducing substance use. They ensure medical treatment for SUD by the medical providers, according to participant desires. They assist with linking to other community substance use and/or harm reduction programs (residential treatment, intensive outpatient, SSPs, etc.). Patient navigators will also conduct outreach to locate missing participants—including homeless encampments and shelters—to continue to provide services. For participants who continue drug use, the patient navigator promotes harm reduction and helps facilitate safer drug use. 3) Housing: For participants experiencing homelessness, patient navigators actively connect participants with local shelters and housing programs and food resources. 4) Access to medical care: patient navigators help participants obtain access to health insurance and other funding sources for ongoing care, especially in the post-intervention period.

#### Social determinants of health

The SIRI team approach to care inherently considers the social determinants of health to mitigate these barriers to meet participants’ needs. Each site’s participants experience different barriers due to unique social, demographic, political, and cultural environments.

#### Post-intervention infectious disease and SUD treatment linkage to care

The SIRI team works with participants to identify and link to post-intervention care. The medical providers determine if participants require follow up infectious disease specialty care for their acute infection. Other common conditions requiring long-term care include SUD, HIV, and hepatitis C, in addition to general primary care needs.

### Control: treatment-as-usual arm

Participants assigned to the TAU arm receive the standard treatment for their SIRI and SUD at each hospital. While TAU may differ between sites, it is typically comprised of a participant cared for primarily by a hospital medicine physician with consultation by infectious diseases and either psychiatry or an addiction medicine physician. If the ID or addiction teams believe post-hospitalization follow up is indicated, each service will follow local protocols for arranging post-discharge continuation of care. This standard of care typically consists of providing participants with an appointment for follow up in an ambulatory care clinic or a list of options for follow-up treatment. Post-discharge care is sometimes provided by the same clinician seen during the hospitalization, but other times it is a colleague or different care team in the community. ID and SUD care are usually provided separately, though some sites may have more novel approaches to co-localized treatment after hospitalization. Some primary care physicians are capable of providing follow-up ID and SUD treatment. Study visits for participants assigned to TAU will include documentation of how care was delivered during the hospitalization and in the post-discharge period.

### Intervention discontinuation and cross-over

The intervention continues until 122 days post-randomization. Because the intervention includes active monitoring of participant medical records and ongoing outreach, the intervention will be terminated early only if a participant withdraws consent from the study or dies prior to day 122. Control group participants are not treated by the SIRI team intervention, as outlined in the intervention manual; however, they are permitted to be treated by clinician members of the SIRI team in non-SIRI team contexts. For example, a SIRI team physician is permitted to be the outpatient HIV provider for a control group participant, as long as the care provided falls within the usual treatments provided by that physician and clinic, outside of the context.

### Outcomes

The primary outcome is a binary measure: a participant is alive with no hospital readmissions 4 months (122 days) post-randomization OR a participant has died or been readmitted to the hospital within 4 months post-randomization. The primary outcome measure is the proportion of those who are alive with no hospital readmission at 4 months post-randomization in the SIRI team intervention compared with TAU. Hospital readmission is defined as either observation or inpatient status in an acute care hospital after discharge from the index hospitalization (i.e., the hospitalization during which randomization occurred). Elective hospital admissions, for example, for planned chemotherapy or elective surgeries, are excluded. Hospital admissions for delivery of a child in pregnant participants will be included as elective admissions. Admission to behavioral health hospitals, medically supervised withdrawal units, or psychiatric-only admissions are also excluded. The primary outcome was chosen to be relevant to patients and healthcare systems. Healthcare utilization outcomes, such as readmission and emergency department visits, will be measured using both EHR data and self-report, confirmed by EHR. At baseline assessment and each follow-up study visit, participants will be asked about healthcare service utilization and if they report receipt of services, a release of information for each relevant institution will be obtained and records requested to confirm self-report. All participants will have the EHR of the study site (*index hospital*) healthcare system queried for health services use. Additionally, any integrated health information exchange services, such as Care Everywhere for Epic, will be queried. Deaths will be determined from EHR data, local medical examiner databases, and information from emergency/secondary contact persons for participants who cannot be located. The secondary outcome related to the primary outcome of the study includes being alive and free from readmission across all study time points (4, 8 and 12 months). Other secondary outcomes are listed in Table 2.

**Table 2 Tab2:** Key secondary outcomes

Outcome	Measure	Time point
Completion of planned antibiotic course	Combination of medical record abstraction and self-report	Assessed at 4-month visit
New or recurrent SIRIs	Combination of medical record abstraction and self-report	4, 8, and 12 months
Non-fatal overdose	Combination of medical record abstraction and self-report	4, 8, and 12 months
Mortality All cause •All cause •Substance use-related (SIRI, overdose)	Combination of medical record abstraction and other sources (e.g., coroner’s report)	Continuous
Substance use severity and frequency	Drug Abuse Screening Test, Alcohol Use Disorders Identification Test, and Addiction Severity Index	4, 8, and 12 months
Initiation of SUD treatment before hospital discharge •MOUD •MAUD	Medical record abstraction	n/a
Initiation of ID treatments before hospital discharge • ART/PrEP • HCV DAAs • Immunizations	Medical record abstraction	n/a
Receipt of post-discharge SUD treatments •MOUD •MAUD •Intensive outpatient •Mutual support •Residential treatment	Combination of medical record abstraction, self-report, and urine test for methadone and buprenorphine	4, 8, and 12 months
Receipt of post-discharge infectious disease treatments	Combination of medical record abstraction and self-report	4, 8, and 12 months
Service utilization measures •Length of stay •Patient directed discharge •Readmissions (count and binary) •ED visits (count and binary)	Combination of medical record abstraction and self-report	4, 8, and 12 months

ED, emergency department; HCV DAAs, hepatitis C virus direct acting antivirals; HIV, human immunodeficiency virus; MAUD, medication for alcohol use disorder; MOUD, medication for opioid use disorder; PrEP, HIV pre-exposure prophylaxis; SIRI, severe injection-related infection; SUD, substance use disorder

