## Methods/Design

### Study design and objectives

The HI-SIRI study is a multicenter non-blinded randomized controlled trial funded by NIDA and conducted in the National Drug Abuse Treatment Clinical Trials Network at 6 hospitals across the U.S. with two parallel treatment arms. The study aims to test the efficacy of an integrated infectious diseases (ID)/substance use disorder (SUD) clinical team intervention on improving health outcomes for PWID hospitalized with SIRIs. The SIRI team provides joint infectious diseases and addiction medicine expertise in a single care team. Participants are identified from the pool of inpatient admissions at participating hospitals. If medically stable, they are invited to provide written informed consent for a brief screening interview. If they screen eligible, provide written informed consent for full study participation, and provide HIPAA Authorization for medical record review, participants complete a baseline assessment (interview, urine drug screening, and medical record abstraction) and are randomized before hospital discharge. Randomization is stratified by 1) hospital site, 2) primary drug (opioid versus non-opioid), and 3) admission to ICU as part of the index hospitalization (ICU versus non-ICU). Participants assigned to the SIRI team meet with SIRI team members approximately daily while hospitalized and approximately weekly post-discharge over the 4-month-long intervention period. The intervention team provides care for infectious diseases and SUD, harm reduction services, patient navigation focused on SUD and social determinants of health, and general medical services throughout the intervention period. Participants assigned to treatment as usual (TAU) receive care and referrals as typically offered in the hospital setting at each site, which might include infectious disease, psychiatry, or addiction medicine consults during hospitalization. Study visits are conducted at baseline, 4 months, 8 months, and 12 months following randomization. The study protocol follows the Standard Protocol Items: Recommendations for Interventional Trials (SPIRIT) Statement (Appendix A). The study was reviewed and approved by the University of Miami Institutional Review Board (UM; IRB#20221134) which serves as the single IRB for the trial and provides regulatory oversight over all the participating sites. The study protocol is available in Appendix B.

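### New or recurrent SIRI and non-fatal overdose could be detected more often in the SIRI arm, because until day 122 the team's own encounters add records in that arm only

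*Protocol article*

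**What the plan says.** Table 2 (Outcomes) lists "New or recurrent SIRIs" and "Non-fatal overdose" as key secondary outcomes at 4, 8 and 12 months. The measure given for each is "Combination of medical record abstraction and self-report". Neither entry requires that the event reach an emergency department (ED) or a hospital.

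The arms differ in how often someone is in a position to write such an event down:

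- **SIRI arm.** Study design and objectives sets the contact schedule: "Participants assigned to the SIRI team meet with SIRI team members approximately daily while hospitalized and approximately weekly post-discharge over the 4-month-long intervention period". Intervention discontinuation and cross-over adds that "the intervention includes active monitoring of participant medical records and ongoing outreach", and runs the intervention to day 122. Under Patient navigator component, "Patient navigators will also conduct outreach to locate missing participants". SIRI team post-discharge care allows clinic, street, home and telehealth encounters.
- **TAU arm.** Control: treatment-as-usual arm describes, typically, an ambulatory appointment or a list of follow-up options. No contact schedule is set.

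Research ascertainment is planned identically for both arms: the same visits and interviews, including an Overdose Information instrument at each follow-up visit (Table 1), index-hospital record and health information exchange queries, record releases, and a study outreach worker. Follow-up assessors are not blinded (Allocation concealment and blinding).

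**The concern.** An abscess or cellulitis treated by the SIRI team outside hospital, or an overdose mentioned to one of its clinicians, can be charted and later abstracted. The same event in a TAU participant has to reach some other source of care whose records are obtained, or be recalled at a visit up to four months later. Box 2 counts cellulitis and skin abscess as qualifying infections, so events that never reach a hospital are plausible.

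The safeguard that the article states is confirmation of self-reported healthcare utilization against records (Outcomes; Discussion). That verifies events that were reported. It does not recover events that were never reported or recorded.

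Study design and objectives presents recurrent SIRI as one of the outcomes meant to show where a difference in the primary outcome comes from. If detection differs by arm, that explanation could go wrong in two ways: a real reduction in infections or overdoses could be hidden, or the intervention could appear to cause them.

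**Working it through.** **Inputs.** The article states no event rate, detection rate or power for these two outcomes, so there is no figure of its own to reproduce on this point. From the article: N = 480, two arms, two-sided alpha 0.05 (stated for the primary test). Assumed: equal allocation, 240 per arm. This fits Table 3, whose rows give power of 0.798 to 0.803 at 240 per arm against the stated 0.80. Also assumed: the true risks and detection probabilities below, and a binary outcome.

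**Contact density.** The intervention lasts 122 days and the article expects at least 3 months of it after discharge. At one contact a week that is about 13 (3 months) to 17 (122 / 7 = 17.4) post-discharge contacts in the SIRI arm, against none scheduled in TAU.

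**Formula.** With true risk p in both arms and detection probabilities s_SIRI and s_TAU, the observed risks are p × s_SIRI and p × s_TAU. The apparent risk ratio is s_SIRI / s_TAU and does not depend on p.

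**Main illustration, p = 25%.**

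- SIRI: 0.25 × 0.95 = 23.75%.
- TAU at 85% detection: 0.25 × 0.85 = 21.25%. Difference 2.5 points; ratio 0.95 / 0.85 = 1.12.
- TAU at 75% detection: 0.25 × 0.75 = 18.75%. Difference 5.0 points; ratio 0.95 / 0.75 = 1.27.

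With 240 per arm and the pooled standard error √(2 × p̄(1 − p̄) / 240):

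- p̄ = 0.225: standard error 0.0381, z = 0.025 / 0.0381 = 0.66.
- p̄ = 0.2125: standard error 0.0373, z = 0.050 / 0.0373 = 1.34.

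The chance of a significant result in the direction of harm is then about 10% and 27%, against a nominal 2.5% in that direction.

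**Range at p = 20%.**

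| Detection SIRI / TAU | Observed SIRI / TAU | Apparent risk ratio | Chance of significant false harm |
|---|---|---|---|
| 0.80 / 0.80 | 16% / 16% | 1.00 | 2.5% |
| 0.90 / 0.85 | 18% / 17% | 1.06 | 4.7% |
| 0.90 / 0.80 | 18% / 16% | 1.12 | 8.4% |
| 0.90 / 0.70 | 18% / 14% | 1.29 | 22% |
| 0.90 / 0.60 | 18% / 12% | 1.50 | 45% |

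**Masking.** A true risk ratio of 0.75 is multiplied by the same detection ratio. At 0.90 / 0.70 it appears as 0.75 × 0.90 / 0.70 = 0.96.

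**The case against.** The strongest reply is that research ascertainment is the same in both arms. SIRI-team contacts are not a listed outcome source. That their notes reach the abstracted record is an inference, though a natural one for charted clinical encounters. Monitoring a chart does not in itself create an event. Events that lead to a hospital encounter should be found by the same queries in both arms. This stands, and it limits the problem to events handled outside acute care.

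A reader might infer that TAU participants have no comparable contact, so that equal true rates would necessarily look like harm. The article does not support this. TAU includes specialist consultation and outpatient follow-up, releases can cover other facilities, and those records can be abstracted too. The gap is one of degree. The z values of 0.66 and 1.34 also show that, under the main assumptions, most such trials would not produce a significant false signal.

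A reader might also infer that the bias stops at day 122 and so distorts the treatment-by-time pattern. That depends on whether the outcomes are cumulative or per interval, which the article does not say. The team also links participants to continuing care, so recording need not fall back at day 122.

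Finally, detailed abstraction rules may sit in the full protocol or the analysis plan, and their absence from an article is no fault. The point rests on what the article does fix: a data source whose density differs by arm. If a fuller document already restricts the sources, one sentence saying so would settle it.

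**Conclusion.** The asymmetry in contact and record generation is documented, and the stated safeguard does not address it. It could bias the comparison of new or recurrent SIRI and of non-fatal overdose against the intervention, mainly at 4 months and mainly for events treated or disclosed outside acute care. Its size cannot be derived from the article. It ranges from nothing, if detection is equal, to an apparent risk ratio of 1.12 to 1.27 under the assumed 25% true risk and 95% against 75% to 85% detection. Larger gaps give larger ratios, up to 1.50 at 0.90 against 0.60.

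The documents support the statement that the data could suggest harm or hide a benefit, not that they would. The primary outcome rests on death and on observation or inpatient stays in acute care hospitals, so it is largely unaffected, and the power statement in Table 3 does not change.

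**What to change.** 1. Record the source of every new or recurrent SIRI and every non-fatal overdose, and flag events known only from SIRI-team clinic, navigator or outreach notes.
2. Prespecify two between-arm analyses of each outcome, reported side by side with a table of event source by arm:
   - (a) events from any source;
   - (b) events only from sources applied identically in both arms, namely acute-care encounters in the index record, the health information exchange and released records, plus the structured study-visit interview.
3. State in advance that (a) may be biased against the intervention and that (b) may favour it, because SIRI-team outpatient care can take the place of an ED visit that would have counted in TAU. For that reason (b) should not be the sole definition. Agreement between the two would be reassuring; disagreement would show how far the conclusion depends on detection.

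The cost is one extra data field, if the forms do not already hold it, and a second analysis of two secondary outcomes. Clinical care, visit schedule and sample size do not change.
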